### Study assessments and procedures

#### Outcome and other non-safety assessments

The data collected during the study visits (see Fig. 1), as described in detail below, and those of the PA are collected and managed using central databases. The Department of Medical Informatics, Biometry and Epidemiology carries out regular data monitoring. Prior to the start of recruitment, all centers and the training institute [name]. [name] receive an initiation including appropriate training measures for data collection, entry, and management using the central databases.

**Fig. 1 Fig1:**
[figure not shown]
Schedule of activities {SPIRIT figure}. *Assessment of physical fitness can be performed at intervals of no more than 4 weeks to the other visit examinations. For patient safety in such cases, a safety questionnaire is collected by the personal trainers and consultation with the lead study center Bochum is obtained prior to implementation. **Assessments V2/V3/V4 ± 2 weeks

Medical history, exacerbation, and physical examination

The medical history will be asked by a questionnaire, including demographic data as well as current medication and therapy. In addition, the PCD exacerbation score [29] will be assessed. A physical examination including height, weight, and BMI is also carried out. The survey and the examination are repeated after 3, 6, and 12 months.

2.Spirometry

PCD is a disease that can affect the lower airways to varying degrees. Spirometry can be used to measure the current lung or respiratory volume. Usable results can be obtained from the age of 5 years. In PCD and other chronic lung diseases, such as bronchial asthma, regular lung function measurements are routine and guide treatment recommendations. Age-adapted standard values exist.

The following values are determined [32, 33]:VCmax (maximum vital capacity)FVC (forced vital capacity)FEV1 (forced expiratory volume in 1 s)PEF (maximum expiratory flow or peak flow)MEF 75/25 (maximum expiratory flow at 75/25% of FVC)sReff (specific airway resistance), if availableTLC (total lung capacity), if available

The examination is repeated after 3, 6, and 12 months. If the lung function measurement coincides with a routine examination, the values from the body plethysmography carried out in this context can alternatively be taken over. At the beginning of the study, the patients are asked to sign a confidentiality agreement for this purpose, which allows the University Children’s Hospital Bochum to request the results of the lung function measurement from the treating physician.

Whenever technically possible, the Lung Clearance Index (LCI) is additionally recorded as part of the lung function examination. The method is established in diagnostics and therapy control in PCD [34–36].

3.Electrocardiogram (ECG)

To identify possible cardiac diseases that could hinder exercise, all test persons will receive a 12-lead ECG at the beginning. This is to detect cardiac arrhythmias, indications of serious conditions such as heart attacks, coronary heart disease, and signs of cardiac stress before the start of the intervention. The examination is only done once at baseline.

4.Assessment of physical fitness (motor test)

The motor test consists of 6 items: standing long jump, push-ups, standing on one leg, sit-ups, forward bend, 10-min run. Most of the components of the motor test have already been administered to children as part of the KIGGS study in the 2007 MoMo project and are thus readily applicable to the assessment of strength, endurance, and mobility in our study population aged 7 years and older [37]. The motor test will be done at the beginning and after 3, 6, and 12 months. The motor test and the other examinations within the framework of one study visit must not be more than 4 weeks apart. If the motor test does not take place on the same day as the other examinations of the study visit, safety questions will be asked before to ensure that the motor test can be carried out in a medically safe manner.

Standing long jump

The test person stands with both feet on the starting line in a shoulder-width stance. Both feet are jumped off and landed at the same time; the distance to the heel of the rear leg is scored. Active arm swing is allowed. The best of three jumps is scored. Measurements are taken in centimeters.

Push-up

The test person starts with the chest at the height of two Theraband stability trainers (ThS) the body is stretched, and the tips of the feet touch the floor shoulder-width apart. The arms are bent with the body stretched until the chest touches the thighs and then stretched again. Bending and stretching are done without rhythm. The number of valid attempts within 30 s is measured.

Single-leg stand

The test person stands at 2 m facing the black sheet and fixes it with the eyes. The time is measured standing on one leg without the playing leg touching the ground or the standing leg moving. Otherwise, evasive movements are allowed. The start is made by lifting the playing leg, after 60 s it is stopped. Both legs are first tested with eyes open, in case of premature termination a second attempt is allowed for each leg. Subsequently, the same test procedure is carried out with blinding by means of a blindfold.

Sit-up

The test person lies on the back with the knees bent parallel (90°), the head resting on the ThS, and the arms stretched out beside the body. The feet are fixed by the test leader. During the test, the upper body is raised until both hands touch the ankles and lowered again until the head touches the stability trainers. The number of completed exercises within 30 s is counted.

Forward bend

The test person stands on a small gymnastic box with his knees stretched out and bends his upper body as far forward and downward as possible in this position. The measurement is taken at the level of the tip of the middle finger without bobbing.

Ten-minute run

The test person runs indoor on a 65-m lap marked with 10 pylons for 10 min on a start signal. The goal is to cover the greatest possible distance. Alternating between running and walking is allowed. The test leader counts the laps and measures the incomplete remaining lap after completion. The distance covered is recorded (= number of laps × 65 m + remaining distance in m).

5.Physical activity

All participants will be given an activity tracker (Garmin Vivofit 4®, instruction manual included) for the study period right at the beginning. The handing over takes place in the context of the first motor test by the personal trainers of the training institute [name]. [name]. They check the correct wear of the activity tracker and assist with the setup. An activity tracker is given to both groups (interventional and control group) to avoid a bias by wearing an activity tracker. The activity tracker is to be worn day and night. The data is automatically synchronized with a central database and stored there in pseudonymized form for data evaluation.

In addition, current PA activity and training wishes are asked through questionnaires as part of the screening visit. The results, together with the results of the motor test, are used to develop the individualized training plan in the intervention group.

6.QoL questionnaire

The questionnaire is an established, validated instrument and used as an outcome parameter in several studies and in the international PCD registry [38, 39]. The QoL-PCD exists for all ages and contains a child version (37 items, 7 scales), parent proxy version (41 items, 9 scales), adolescent version (43 items, 7 scales), and adult version (49 items, 10 scales) [38–40]. The QoL-PCD scales include physical functioning (primary outcome); the other ones are secondary endpoints (e.g., emotional functioning, treatment burden, social functioning, role functioning, health perception, vitality). With the QoL-PCD, we choose an internationally validated PCD specific tool for different age groups [38, 39]. Filling in the questionnaire takes little time and will be tablet based or may be done at home via an individual link. One week before randomization, the participants and, in the case of minors, also the guardians receive a link with which they answer the questionnaire directly online in the central database. In addition, the questionnaires are recorded during the V2–V4 visits after 3, 6, and 12 months.

#### Safety assessments

Participant safety is taken very seriously in this study.

The individual risk in the study corresponds to the usual risk of PA which is recommended by guidelines as part of the standard therapy. This includes injuries, overuse injuries, cardiovascular events, and psychological risks such as sport addiction [22, 23, 41–44]. Other rare risks—seen sporadically in studies with PA in pwCF (or asthma bronchiale [24])—could be the occurrence of pneumothoraxes, when starting physical activity too early after infections, and other pulmonary complications like bronchial obstruction or hemoptysis [8, 24]. However, the increase in PA also offers many advantages for pwPCD.

Study participants are given the possibility to improve their health-enhancing PA by regular qualified support, and thus to improve their lung function, physical fitness, and participation in everyday life [6, 9, 43, 45–47]. In the middle term, we expect an improvement in treatment adherence and quality of life with a consequent slowing of the progression of the chronic disease PCD. The long-term benefit for all pwPCD would be the establishment of guided PA in the therapy and rehabilitation guidelines. In the risk–benefit analysis, the benefits for the participating patients clearly outweigh the risks.

To minimize the risks for participating patients, they are examined in detail for contraindications to participation in a PA program (see schedule of activities and “Exclusion criteria”) and receive comprehensive information when not to take part in PA. In addition, the focus of this study is on health-enhancing, individually adapted physical activity and not on physical exertion. The participants do the PA they prefer at their own pace under the close guidance of the qualified personal trainer. For this reason, the intervention group is questioned weekly by means of a standardized questionnaire about the occurrence of potentially critical complaints in the context of PA by the respective personal trainer. If one of the participants answers at least one of the questions in the lower third of the Numeric Analog Scale [1–4, 21, 29, 37, 40, 48, 49], which is handed out and explained at V0, PA will be discontinued immediately until medical clearance by the lead study center in Bochum is obtained. A standardized safety questionnaire must also be completed before the motor test that is part of the study visits. If there are indications of a medical concern, the lead study center Bochum will be contacted and if there is any doubt the test will not be performed.

An assessment of adverse events (AE) and serious adverse events (SAE) will be performed in the intervention and control group to evaluate the safety of the study intervention. For further details see below and under “Safety oversight.”

#### Adverse events and serious adverse events

In the following, we define the AEs and SAEs to which we are limited in this study due to the chosen intervention and the clinical characteristics of PCD. They comprehensively recognize both the expected risks and serious complications.

Adverse event (AE)Any unplanned doctor contactPulmonary exacerbation or other pulmonary complications (obstruction, etc.)New antibioticsAccident during physical activity without hospital contactMedically justified discontinuation of physical activity (single occurrence)Discontinuation of intervention due to a medical cause

Serious adverse event (SAE)DeathAny unplanned hospitalization or hospital presentation

For adverse events (AEs), the following guidelines will be used to describe severity.Mild—Events require minimal or no treatment and do not interfere with the participant’s daily activities.Moderate—Events result in a low level of inconvenience or concern with therapeutic measures. Moderate events may cause some interference with functioning.Severe—Events interrupt a participant’s usual daily activity and may require systemic drug therapy or other treatment. Severe events are usually potentially life-threatening or incapacitating. Of note, the term “severe” does not necessarily have to be identical with “serious.”

All adverse events (AEs) will have their relationship to study procedures, including the intervention, assessed by appropriately trained clinicians (pediatric and internal medicine) based on temporal relationship and his/her clinical judgment. The degree of certainty about causality will be graded using the categories below.Related—The AE is known to occur with the study procedures, there is a reasonable possibility that the study procedures caused the AE, or there is a temporal relationship between the study procedures and the event. Reasonable possibility means that there is evidence to suggest a causal relationship between the study procedures and the AE.Not related—There is not a reasonable possibility that the study procedures caused the event, there is no temporal relationship between the study procedures and event onset, or an alternate etiology has been established.

During each study visit (V2–V4), a standardized query (CRF) is made by means of questionnaires of the AEs and SAEs defined above. In addition, all participants are encouraged to report unplanned hospitalizations (SAEs) to their supervising study center within 48 h.

Information to be collected includes event description, time of onset, clinician’s assessment of severity, relationship to study procedures (assessed only by those with the training and authority to make a diagnosis), and time of resolution/stabilization of the event. All AEs occurring while on study will be documented appropriately regardless of relationship. All AEs will be followed to adequate resolution.

All (S)AEs are documented in the central study database by the responsible study center. If an AE or SAE is recorded in the central database, the study team of the lead study center Bochum is automatically informed. In addition, the SAE report can be forwarded to the lead study center via fax. The study team will then contact the registering study center and the subject to obtain further information. In the case of SAEs, the SAE board is immediately involved. The intervention will be interrupted until the final clarification of whether there is a risk for the participant by continuing the intervention. The lead study center in Bochum will inform the participants as soon as possible whether the intervention can be resumed.

The lead study center Bochum will record events with start dates occurring any time after informed consent is obtained until the last day of study participation. The documents are submitted to the DSMB once a year for further review.

The local study management at each site is responsible for truthfully documenting all AEs and SAEs during study visits and for notification also in between in the central database. The lead study center in Bochum and the PI receives an automated notification from the central database upon registration and must check it immediately. SAE reports are forwarded to the SAE board within 72 h. After the final assessment of the event, the documents are collected and forwarded bundled to the DSMB once a year by the PI or a named representative of the leading study center in Bochum. In the event of an accumulation of study-relevant SAEs, early convening of the DSMB and notification to the relevant ethics committee will be made by the PI. The assessment of the event is documented in the central database by the study team at the Bochum University Children’s Hospital.

As part of the underlying disease, pulmonary exacerbations and associated doctor contacts or unplanned hospital stays are common. If this constellation emerges during the examination by the central study center, it is not necessary to involve the SAE board for verification. The assessment and documentation are then carried out by the study team from Bochum directly in the central database. The DSMB is regularly informed by the annual report. If there is an increase in pulmonary exacerbations in a study center or the study, the PI or a named representative is obliged to inform the SAE board separately within 72 h. Depending on the assessment of the SAE board, an early notification to the DSMB as well as to the ethics committee responsible will also be made by the PI in this case.

After assessing the event, the study team from Bochum will contact the participant by telephone to discuss further procedures regarding the study. If pathological findings are detected during the study visits, the participant will be informed directly orally about the findings and a recommendation for further (subject-specific) clarification will be made. If requested, the participant may be provided with a copy of the examination results for the doctor providing further treatment.

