#### Study intervention discontinuation and participant discontinuation/withdrawal

The occurrence of diagnoses or examination results listed under “Exclusion criteria” or a positive answer in the weekly safety query described under “Safety assessments” will lead to an immediate discontinuation of the intervention.

When a subject discontinues from the PA program but not from the study, remaining study procedures will be completed as indicated by the study protocol. In individual cases, a decision may be made to continue the study without participation in the assessment of physical fitness.

In addition, all subjects are explicitly informed that if they have any doubts about PA and exercising, they should discontinue and contact the supervising or leading study center. Participants will be informed that if one of the following symptoms occurs, PA must be interrupted, or no further PA should be done until medical clarification is obtained:Fever or other infections accompanied by a feeling of illnessAcute pulmonary exacerbationSevere joint, back, or head pain during or immediately after exerciseChest pain or left arm painDizziness/syncopeShortness of breath (beyond expected level) or hyperventilationHypoglycemiaPersistent palpitations or heart palpitations after exercisePacemaker/ICD depending on type of PA

Participants are free to withdraw from participation in the study at any time upon request without giving reasons and without suffering any disadvantage, as stated to them prior to informed consent. Participants will be given the choice as to whether their withdrawal will only be from further contact from the trial team or withdrawal of all their unanalyzed data.

An investigator may discontinue a participant from the study for the following reasons:Lost-to-follow up; unable to contact subject (see below)Any event or medical condition or situation occurs such that continued collection of follow-up study data would not be in the best interest of the participant or might not be possible, e.g., longer inpatient stay

The reason for participant discontinuation or withdrawal from the study will be recorded on the study discontinuation form. Subjects who sign the informed consent form and are randomized but do not receive the study intervention may be replaced.

A participant will be considered lost to follow-up if he or she fails to return for one scheduled assessment and study staff are unable to contact the participant after five attempts.

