#### Safety analyses

Analysis of safety endpoints will be performed in the safety analysis set. Adverse events will be analyzed as number and percentage per group. Events leading to a discontinuation of the intervention or withdrawal from the study will be tabulated.

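### The closed adverse event list is called comprehensive, but it has no direct category for overuse injury or exercise-related psychological harm, both of which the protocol names as expected risks

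*Protocol article*

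**What the plan says.** Under Adverse events and serious adverse events, the protocol article closes the list of events: "we define the AEs and SAEs to which we are limited in this study". It then states what the list achieves: "They comprehensively recognize both the expected risks and serious complications".

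The six AE categories are, in paraphrase:

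- an unplanned contact with a doctor
- a pulmonary exacerbation or other pulmonary complication
- a new course of antibiotics
- an accident during activity that does not reach hospital
- a single medically justified stop of physical activity
- "Discontinuation of intervention due to a medical cause"

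The two SAE categories are death and any unplanned hospital stay or presentation. The standardized query at V2 to V4 asks about the events so defined.

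The expected risks appear under Safety assessments: "This includes injuries, overuse injuries, cardiovascular events, and psychological risks such as sport addiction". Rarer pulmonary complications follow. The same section describes a weekly check in one arm only: "the intervention group is questioned weekly by means of a standardized questionnaire about the occurrence of potentially critical complaints". A positive answer has a consequence: "PA will be discontinued immediately until medical clearance by the lead study center in Bochum is obtained".

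The section on discontinuation lists symptoms for which "PA must be interrupted, or no further PA should be done until medical clarification is obtained". For analysis, Safety analyses says: "Adverse events will be analyzed as number and percentage per group".

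**The concern.** One section names the risks of the programme. Another fixes a closed list of events and says that it covers those risks. The two do not match for overuse injury or for psychological harm.

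Table 1 makes safety a secondary objective and says that the safety of the intervention has to be established. Overuse and unhealthy attachment to exercise are harms that an activity programme could itself produce. The programme sets no minimum dose, lets participants expand it at any time and enrols from age 7. If these harms are recorded only when they have a medical consequence, a balanced AE table would be silent on the milder or undeclared cases. A reader who trusted the coverage claim would take that silence as evidence of absence.

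**Working it through.** No arithmetic applies, and the plan gives no figure to reproduce. The check takes each risk named under Safety assessments and asks which listed category would record it, directly or through its consequences.

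1. **Acute injury.** The accident category records it directly when it does not reach hospital, and the SAE category when it does. Covered.

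2. **Cardiovascular events.** These have no category of their own, but they would normally lead to a doctor contact (AE) or a hospital presentation (SAE). Chest or left arm pain, dizziness or syncope, and persistent palpitations are also on the list of symptoms that interrupt activity. A single medically justified stop is itself an AE, and the wording of that category does not require a doctor contact. Largely covered.

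3. **Overuse injury.** A gradual overuse complaint is not plainly an accident. It enters the list if it leads to a doctor contact or a medically justified stop. The musculoskeletal entry on the symptom list covers only severe joint or back pain during or immediately after exercise. A milder or slowly developing complaint that the participant manages alone fits no category. Partly covered.

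4. **Psychological risk such as sport addiction.** No category names it and no symptom on the interruption list points to it. It is recorded only through a doctor contact, a hospital presentation or a stop on medical grounds. Largely uncovered.

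5. **Pulmonary complications.** The pulmonary category or a hospital presentation records them. Covered.

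Of the four non-pulmonary risk groups, two therefore have a gap (items 3 and 4).

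Three further points bear on whether something else closes it:

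- The V2 to V4 query is tied to the defined events, so unlisted ones are not solicited.
- Unanticipated problems covers what is unexpected in nature, severity or frequency. Risks named in advance are not unexpected in nature, so that section is not a reliable backstop.
- The severity scale includes mild events that need little or no treatment. Mild events are thus within scope, yet a mild self-managed overuse complaint has no category in which to be graded.

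The indirect routes are also wider in one arm. The weekly safety questionnaire runs only in the intervention group, and discontinuation of the intervention can occur only there. In both arms, a case with no medical consequence stays outside the list.

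**The case against.** **Defining events by consequence is a defensible choice.** The trial is unblinded and the activity is guideline-recommended. Soft, self-reported items may be answered differently by the two arms, since only one is coached weekly. Items added after recruitment began will also be collected unevenly. This stands as a cost of the fix. It does not rescue the statement that the list is comprehensive.

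**Other records exist.** Weekly coaching conversations are documented and are meant to determine safety. The weekly questionnaire asks about potentially critical complaints. The definition of unanticipated problems expressly mentions psychological harm. All this is true, so some cases may be known to the study team. But the coaching and weekly-questionnaire records exist in one arm only, and none of the three is an entry in the per-group AE table. The article also says that all AEs are documented whatever their cause, but there AE means the events on the list.

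**The questionnaire items and the full protocol are not shown.** They may add detail. The article itself nevertheless states the closed list, the coverage claim and the scope of the query, and these can be compared as they stand.

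Two stronger readings are tempting, and the documents do not support them:

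- A reader might infer that exertional cardiac symptoms are omitted too. The risk named is cardiovascular events, and both the events and the listed symptoms have routes into the list, as shown above. What remains is an ambiguity: the article does not say whether a stop made by the participant alone is medically justified.
- A reader might infer that overuse injuries seen by a doctor disappear among contacts for infection. The article requires an event description, a severity grade and a judgement of relationship to study procedures for each event, so recorded cases can be separated. The layout of tables may properly be left to the analysis plan.

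**Conclusion.** The point holds in a limited form. The list is closed and described as comprehensive for the expected risks, but it has no direct category for two risks that the protocol itself expects. Followed exactly, the plan would not record overuse injuries or exercise-related psychological problems that lead to no doctor contact, hospital presentation or medically justified stop. The per-group AE comparison therefore cannot support a conclusion on these two risks in full.

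The size is two of four non-pulmonary risk groups: one partly covered, one largely uncovered. The documents give no incidence for either, so any count of missed events would rest on an assumed rate, and the conclusion does not need one. The cases at issue are likely to be mild or undeclared, because the more serious ones should reach a doctor or hospital.

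The conclusion assumes that a gradual overuse complaint is not an accident in the sense of the list, and that the V2 to V4 query asks about nothing beyond the defined events, as the article says.

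**What to change.** Reconcile Safety assessments with Adverse events and serious adverse events as follows:

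1. Add two items to the list and to the existing V2 to V4 query, identically worded in both arms: (a) an activity-related injury or overuse complaint, with or without a doctor contact; (b) an exercise-related psychological problem.
2. State whether a stop of activity made by the participant alone counts as medically justified for AE recording.
3. If the list is to stay unchanged, delete the claim of comprehensive coverage and limit the safety conclusion to the events recorded.

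The first two steps need a short amendment and two questions in a query that already exists, with no new visits. AE counts will rise somewhat, and self-report in an unblinded trial may differ between arms. Recruitment began in March 2024, so the items will be missing for visits already completed, and the report should say so. Only recording and reporting change; no rule for stopping or resuming activity is touched.
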